#### Power calculations

In order to explore power of the ITS analysis to detect changes in health outcomes we have consulted a range of epidemiological studies and systematic reviews, along with identification of relevant intervention studies for effect sizes. Our own research has found that a 10μg/m3 increase in NO_2_ is associated with a 9% increase in the odds of low birthweight, while a 5μg/m3 increase in PM2.5 is associated with an 18% increase in odds of low birth weight [58]. For other health outcomes, systematic reviews have shown a 10μg/m3 increase in NO_2_ to be associated with increases in respiratory disease hospital admissions ranging between 0.57-3.5%, and a 0.66% increase in admissions for cardiovascular admissions, with stronger effects among children and the elderly [59–63].

Recent intervention studies (reviewed earlier) offer no consistent results. Based on the evidence reviewed and working on the assumption the B-CAP will reduce NO_2_ by between 12-18μg/m3 we have estimated a 5% reduction in health outcomes (emergency / GP attendances and incidence related to both respiratory and cardiovascular outcomes); and a 2% reduction in adverse birth outcomes. A 5% reduction in emergency attendances in relation to respiratory and / or cardiovascular illness would likely have substantial cost-savings for the NHS [64].

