We have reviewed methods to inform power calculations; there are no accepted guidelines for calculating power in ITS designs [65, 66]. Power is dependent on a variety of factors including the length of the time series (with some suggesting 100 observation points required for correct model identification), [67] the balance of time points before and after the intervention, the expected effect size, the extent of autocorrelation between the data points, and sample size per time point. Power increases in a balanced ITS design; in WP3 our proposed study would increase the power by ensuring roughly equal number of data points for the 3 years pre- and 3 years post-implementation. We illustrate the potential power of our analyses for our primary outcome, respiratory health (measured as emergency/GP admissions): in pilot analysis of a subsample of our connected data set (*N* = 316,585, assessed between Jan 2016-Dec 2018) we observed an average of 380 respiratory attendances per week suggesting adequate counts per observation period. Using weekly counts will give us a total of 312 observation points over a 6 year period. Guidance from simulations of Winquist et al. [66] suggests we will have > 90% power to detect a 2% reduction in admissions. For our secondary outcomes (cardiovascular/birth) we will assess counts either weekly or monthly depending on prevalence. Using monthly events a balanced design would give us 72 evenly distributed observations points. We will explore increasing the baseline intervention trend period by 28 months (e.g. 5 years pre-implementation) to ensure we can maintain 100 observation points (which is acceptable if there are no other major changes in pre-intervention trends in that time period) [65].

In WP3B we will focus only on respiratory attendances within the BiB cohort using similar methods. For these analyses we will have fewer events per observation period and so will perform analyses using either weekly or monthly counts.

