Given the seasonal variation in respiratory outcomes and pollution, data will be adjusted for seasonality. We will also assess the models for residual autocorrelation and apply ARIMA methods as necessary. We hypothesize that the B-CAP will lead to a larger decrease in outcomes for those living in more deprived areas and by ethnicity and will examine these through interaction terms and stratified analyses. We will consider a series of sensitivity analyses by varying model assumptions. We expect air pollutants to decrease the most within the CAZ boundary compared to without and will examine the impact of spatial variation on outcomes. We will test our assumption that the effects of the implementation of the CAZ are gradual, by altering the length of the third segment based on dates of when implementation activities were initiated. We will also assess lagged effects between exposures to air pollution and health outcomes.

ITS is a strong evaluation design when randomization is not possible as post-intervention trends can be compared to trends prior to the interruption of the intervention. We will strengthen this design through the inclusion of a non-equivalent control (NEC) outcome (superficial head injuries) which will not be affected by the intervention (CAZ) to control for possible concurrent events. Previous studies utilizing a NEC have used finger wounds [31]); we chose superficial head injuries given the higher number of cases per month compared to other potential injuries. A change in the outcome of interest following implementation of the CAZ with no change in the NEC would increase our confidence that the changes observed were a result of the intervention.

For WP3B, we will conduct detailed analyses on health inequalities using data from the BiB cohort, which has individual, in addition to area level, information on socioeconomic status. We will replicate analysis on respiratory outcomes looking at both combined respiratory morbidities and separately at asthma/wheeze, exploring multi-dimensional measures of socio-economic status, [68] ethnicity, deprivation, employment, religion, education and social capital using the PROGRESS framework as a guide to selecting relevant indicators [57].

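### The head-injury control outcome is to be read side by side with respiratory attendances, which does not by itself control for a concurrent event; the two changes should be contrasted directly

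*Protocol article*

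**What the plan says.** In the protocol article, Work package 3, Analysis methods, the interrupted time series is strengthened with an NEC outcome, superficial head injuries, "which will not be affected by the intervention (CAZ) to control for possible concurrent events". The choice is explained by volume: "we chose superficial head injuries given the higher number of cases per month compared to other potential injuries". No count is given.

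The interpretation is one sentence: "A change in the outcome of interest following implementation of the CAZ with no change in the NEC would increase our confidence" that the observed changes came from the intervention. The article does not define no change, and it mentions no contrast between the two series.

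Under Power calculations, for the primary outcome, "we observed an average of 380 respiratory attendances per week suggesting adequate counts per observation period", in a pilot subsample of 316,585 people. The design is described as "Using weekly counts will give us a total of 312 observation points over a 6 year period", and cited simulation guidance "suggests we will have > 90% power to detect a 2% reduction in admissions". The size of effect expected is in the same section: "we have estimated a 5% reduction in health outcomes" for respiratory and cardiovascular attendances.

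**The concern.** A control outcome can deal with a concurrent event only if the change in the outcome of interest is set against the change in the control. Finding a change in one series and none in the other is not evidence that the two changes differ, because the series may carry very different amounts of information.

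Take an event with nothing to do with the clean air plan, such as a shift in care-seeking or in access to A&E, that lowers both series by the same percentage. A large respiratory series will show it. A small head-injury series may not. The result is then exactly the pattern that the article says would raise confidence in the plan. This can happen even if head injuries are a perfectly valid control, wholly unaffected by the zone.

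The NEC is the one element that the article assigns to concurrent events at switch-on, and the health work package names no control city. A check that can succeed because its control is imprecise would give unearned reassurance about attribution.

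**Working it through.** **Inputs.** Respiratory count 380 a week, 312 weeks split as 156 before and 156 after, relevant effect 5% (all from Power calculations). Assumed, because the article does not give them: an NEC count of 10 to 380 a week, Poisson variance, a two-sided 5% test, and no change read as a non-significant NEC result.

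**The plan's own figure.** For a 2% reduction in a simple before/after contrast, SE of the log rate ratio = √(2/(380 × 156)) = √(2/59,280) = 0.0058. |ln 0.98|/SE = 0.0202/0.0058 = 3.48, so power = Φ(3.48 − 1.96) ≈ 94%. This agrees with the stated figure of over 90%. The same calculation gives 52% when there is an underlying trend and the effect is a slope change averaging 2%. The simple contrast is therefore the favourable case.

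**Shared 5% fall, no plan effect, simple contrast.** With N = weekly count × 156, SE = √(1/N + 1/(0.95N)), and power = Φ(|ln 0.95|/SE − 1.96), where |ln 0.95| = 0.0513.

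- Respiratory: N = 59,280, SE = 0.0059, ratio 8.7, power about 100%.
- NEC at 25 a week: N = 3,900, SE = √(1/3,900 + 1/3,705) = 0.0229, ratio 2.24, power Φ(0.28) = 61%, missed 39%.

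The chance of the supportive pattern is respiratory power × (1 − NEC power):

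| NEC per week | NEC SE | NEC power | Supportive pattern |
|---|---|---|---|
| 10 | 0.0363 | 29% | 71% |
| 25 | 0.0229 | 61% | 39% |
| 50 | 0.0162 | 89% | 11% |
| 80 | 0.0128 | 98% | 2% |
| 100 | 0.0115 | 99% | under 1% |

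The miss rate falls below 20% at about 40 a week.

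**Segmented models.**

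- Two segments with an underlying trend and a slope change averaging 5%, the form of effect that Analysis methods expects: NEC power is 13%, 22%, 38%, 65% and 89% at 10, 20, 40, 80 and 150 a week. Respiratory power is 99.9%, so the supportive pattern occurs about 87%, 78%, 62%, 35% and 11% of the time. NEC power reaches 80% at about 115 a week.
- The four planned segments, each with level and slope, two seasonal harmonics and switch-on assumed in late September 2022: for a 5% shift in the level term at switch-on, the pattern occurs 82%, 77%, 70% and 56% of the time at 10, 25, 50 and 100 a week, and 10% at 380. These figures test an isolated level term, which is not the slope change the article expects, so they are an unfavourable bound and not a forecast.

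**Direct contrast.** The log of the ratio of the two rate ratios has SE = √(SE_NEC² + SE_resp²). Under a shared fall the true ratio is 1, so the test rejects 5% of the time at any NEC count. For a true 5% plan effect and no shared event, at 10 a week SE = √(0.0363² + 0.0059²) = 0.0367 and power is about 29%; at 25 a week SE = 0.0237 and power is about 58%.

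**What the NEC interval can show.** If the NEC truly does not change, its 95% half-width on the log scale is 1.96 × √(2/N): about 7.0% at 10 a week, 4.4% at 25 and 3.1% at 50. At 10 a week, an estimate of no change could not exclude a 5% fall.

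**The case against.** The strongest reply is that the article does not state the rule simulated here. Its sentence describes corroboration: confidence would rise. A reader might infer that a respiratory change is accepted as the plan's effect whenever the NEC is flat, but the text sets no such gate. A reader might also infer a significance test and a sparse NEC series. Neither is documented: no test is named, and quoting volume per month does not show that the count is low. The authors considered volume when choosing the outcome. The 380 a week comes from a subsample, so full-dataset counts would be higher for both series. In the simple contrast the problem has practically gone by 80 to 100 NEC events a week. All of this stands, and it limits the claim.

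The NEC is also not the only safeguard. The pandemic is handled through change points, outcomes inside and outside the zone will be examined, and sensitivity analyses and a synthesis across work packages are planned. It would therefore be wrong to say that the main causal claim rests on this check.

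Finally, a margin or a joint model is ordinary analysis-plan content, the article is condensed, and no analysis plan is shown. Silence on those details is no fault. What remains is what the article does state: a purpose, controlling for concurrent events, paired with a reading that does not achieve it.

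**Conclusion.** The point holds in a limited form. Reading a respiratory change beside an unchanged NEC does not control for a shared event, and how far it misleads depends on an NEC count that the article does not give. For a shared 5% fall with no plan effect, the supportive pattern would arise about 71%, 39%, 11% and 2% of the time at 10, 25, 50 and 80 NEC events a week in the simple contrast, and more often in segmented models. These figures rest on Poisson variance and on reading no change as non-significance. Variance above Poisson, or autocorrelation, would lower the power of both series.

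The documents do not show that the NEC is in fact sparse, that a shared event would usually be missed, or that the NEC result decides the conclusion. No stated figure is wrong: the claimed power reproduces under the simple contrast. This is a choice of reading that can be improved cheaply.

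**What to change.** Keep the respiratory-only interrupted time series as the primary estimate. For the concurrent-event question:

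- Fit the respiratory and NEC series in one segmented model with series-by-level and series-by-slope terms at switch-on.
- Report the ratio of the respiratory change to the NEC change, each as predicted versus counterfactual, with its 95% interval. Base the statement about concurrent events on that interval.
- Report the NEC's own estimate with its interval, and state its expected count in advance.
- Call the check inconclusive when the NEC interval does not exclude a change of the 5% size assumed under Power calculations.
- State the assumption that a concurrent event moves both series by a similar percentage.

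The cost is some analysis-plan wording and one joint model on data already due to be extracted. The price in precision is real if the NEC is small: about 29% power for a true 5% effect at 10 NEC events a week and 58% at 25, in the simple contrast. At such counts the check may well be reported as inconclusive, and the expected count would show this beforehand.

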### Workpackage 4: Cost effectiveness analysis

Following guidance on appropriate methods for economic evaluation alongside natural experiments, [69] and our recent work, [70] we will perform a multi-sectoral cost-effectiveness analysis to determine value for money of the B-CAP considering a range of costs across sectors, and quantifying outcomes in terms of quality adjusted life years (QALY). Key economic outcomes will include healthcare resource use and costs, private economy and LA costs, quality adjusted life years, distributional effects (all at 3 years follow up). The comparator in our evaluation will be pre B-CAP implementation outcomes and costs. Our evaluation will explicitly consider the costs and outcomes for a range of decision makers (for example, health care, private economy and local authorities) and sectors (e.g. business, health), along with different socioeconomic groups to capture distributional effects (e.g. burden of paying charge) which may impact on inequalities. We will consider the cost of delivering the interventions in the B-CAP, and any cost-offsets, for example due to reduced GP consultations and hospital admissions.

We will consider the relevant costs, opportunity costs and benefits for each decision maker/sector involved. Potential sources of double counting will be explored and adjusted for where possible. We will then summarise the impacts on each sector, for example, the impact on health and health care costs from an NHS perspective. An aggregate approach across all sectors will also be considered with costs and benefits brought together to estimate the societal benefit of CAZ, which can be expressed as Net Benefit (benefits net of any opportunity costs). Different time horizons will be considered for the analysis to account for budget cycles, differences by sector, i.e. cost may have to be justified over a short time period for some sectors, including local authorities. .

The overall cost of the B-CAP will be estimated, and we will show how much of this cost falls on local authorities, and how much falls in the wider economy where they cascade to individuals and private companies (e.g. cost of charge for non-compliant vehicle). The costs of the B-CAP to the local authority and the wider economy, will be assumed to continue for as long as the intervention is applied. Wider societal benefits will be considered by exploring any impacts on productivity and individuals’ private consumption related to health status, i.e. a health event incurs a productivity loss and associated cost to the economy in terms of lost wages and may reduce an individual’s private expenditure [71].

The analysis of CBradford data will also allow us to consider the change in health across different socioeconomic groups (defined by the Index of Multiple Deprivation of the population of the area in which people live at Lower Layer Super Output Area).

Distributional cost-effectiveness analysis [72] will be used to evaluate the impact the B-CAP has on the socio-economic distribution of health, reflecting both the direct impact of the B-CAP on the health of different socioeconomic groups and the impact on heath in terms of forgone health from opportunity costs resulting from any costs associated with the B-CAP. The value for money from the B-CAP can be evaluated considering both goals of improving total population health (net benefit in terms of QALYs for the population of Bradford) and reducing inequalities (e.g. reducing the gap in health outcomes between the most versus the least deprived groups in Bradford, or between ethnic groups).

The within study analysis will utilise data from WP3 with a 3 year follow up. In addition, the economic evaluation will extrapolate any changes in short term outcomes to longer term costs and consequences using a decision analytic model. For changes in short term health outcomes, for example cardiovascular, respiratory disease and incidence of pre-term births, these health states will be extrapolated over the longer (life) time, to determine the impact of these conditions on quality adjusted life years (QALY) and costs. This lifetime modelling work will also reflect costs to all sectors impacted by the CAZ and the impact on inequalities. The model will also reflect the sampling uncertainty in the evidence available from WP3, the costs of the CAZ from WP1 and any external evidence used to extrapolate health states. We will use probabilistic cost effectiveness analysis to establish the amount of uncertainty in our value for money assessments.

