### Work package 3: Health impacts

We will assess the extent to which implementation of the B-CAP impacts on health outcomes, using a quasi-experimental interrupted time series design with our Connected Bradford (cBradford) and BiB data sets. We will compare trends of health outcomes collected for 3 years pre, and 3 years post implementation (minimum 6 years data). Using the cBradford dataset, in WP3A we will explore changes in a range of health outcomes across the life-course up to 3 years post implementation using a segmented regression approach. Drawing on the PROGRESS framework for health equity [57], in WP3B we will investigate in detail the impact of the B-CAP on health inequalities, considering a wide range of characteristics (for example, household-level SES and ethnicity), focusing on respiratory health outcomes for 13,500 children in our BiB data set.

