We will examine time-series line plots of the health outcomes to aid identification of underlying trends and seasonal patterns of the data. As the outcomes are counts, the Poisson link function will be used in the regression model. Models will be adjusted for age, sex, ethnicity, and measures of SES such as IMD. The coefficients from this regression can be used to estimate the intervention effect (the absolute difference between the predicted outcome based on the B-CAP and its counterfactual value, i.e. the expected values for level and trend if the intervention had not occurred. We will account for the disruption caused as a result of the COVID-19 pandemic, and the subsequent changes in behaviour including alterations to travel behaviour and A&E and GP attendances, through the selection of change points used in the segmented regressions. In England, the first lockdown was implemented on the 23rd of March 2020 and the third ended on the 31st July 2021. We will therefore consider four segments for our analysis: (1) the period prior to the first national lockdown from when clinical data of sufficient quality was available (October 2017 – March 2020); (2) the period spanning the lockdowns (March 2020 – August 2021); (3) the period encompassing the preparation phase for the CAZ (August 2021 - CAZ switch on, this includes other activities within the B-CAP including provision of grants for vehicle upgrades); (4) the period post ‘switch on’ of the charging CAZ). We will conduct an interim analysis at 12 months post-implementation and re-examine analyses 3 years post-implementation.

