## Discussion

We have a rare opportunity to conduct a quasi-experimental evaluation of a city-wide air quality intervention (Bradford Clean Air Plan: B-CAP), which includes implementation of a charging Clean Air Zone (CAZ) to determine its impact on air quality, health outcomes and inequalities across the life-course. Our proposed study is unique in that it additionally includes a full process and implementation evaluation in addition to planned cost-effectiveness analysis. This will provide rich learning to other areas who are planning to implement this type of approach to improve air quality.

The COVID pandemic has been a major challenge to both implementation of B-CAP and the research programme, causing delays in fieldwork and implementation of the B-CAP. Data collection started in Summer 2021 after lock down periods instigated by the pandemic were lifted, approximately 12 months later than planned. However, the corresponding delay in implementation of the plan has meant we have still been able to collected baseline data. We have had to amend our data collection tools and analysis plans to take into account changes in travel behaviour as a result of the pandemic (for example, reduction in travel during initial lockdown periods resulting in improved air quality for a temporary period, decreased use of public transport as lockdown restrictions eased) as well as periods of reduced health service use affecting measurement of our primary outcome. A strength of our study is its use of routinely collected data available from the cBradford dataset which has remained unaffected by the pandemic, and our use of an interrupted time series design with segmented regression break points which means we are able to isolate ‘atypical’ periods during the pandemic lockdown and account for these in our analyses.

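### The economic evaluation names the pre-B-CAP period as its comparator, which does not match the projected no-intervention counterfactual that defines the health effect in work package 3

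*Protocol article*

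**What the plan says.** Protocol article, Workpackage 4: Cost effectiveness analysis, fixes the comparator for the whole economic evaluation in one sentence: "The comparator in our evaluation will be pre B-CAP implementation outcomes and costs". It covers costs as well as outcomes. It does not mention trend, season, the pandemic or a counterfactual.

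Work package 3, Analysis methods, defines the effect as the difference between the predicted outcome under the B-CAP and "its counterfactual value, i.e. the expected values for level and trend if the intervention had not occurred". It splits the series into four segments: before the first lockdown (from October 2017), the lockdowns, the preparation phase (from August 2021, already containing B-CAP activity such as vehicle grants), and the period after charging starts.

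Two sentences in the work package 4 section link it to work package 3: "The within study analysis will utilise data from WP3 with a 3 year follow up" and, about the long-term model, "The model will also reflect the sampling uncertainty in the evidence available from WP3". Neither says that the ITS contrast is the quantity carried over.

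The Discussion acknowledges "periods of reduced health service use affecting measurement of our primary outcome". It says that the segmented break points allow for the atypical periods, but does not apply this to the economic comparator.

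**The concern.** The two contrasts agree only if nothing but the B-CAP changed between the pre-period and the post-period. The protocol itself says otherwise. Health service use fell during the pandemic, and the preparation phase counts as pre-implementation (the Abstract defines implementation as the date charging goes live) although parts of the plan were already running.

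If the comparator is applied as written, depressed lockdown attendances lower the baseline. Averted NHS use and its cost-offsets are then understated, or appear as an excess. Secular trend could push the result either way. If the lockdown fall differed between deprivation groups, the distributional results would be affected too. The within-study results are then extrapolated over a lifetime. Probabilistic analysis carries sampling uncertainty forward, but it does not correct a comparator that measures the wrong contrast.

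**Working it through.** **Inputs from the protocol**
- Lockdown dates (work package 3, Analysis methods): "the first lockdown was implemented on the 23rd of March 2020 and the third ended on the 31st July 2021".
- Pre-period, general statement (Work package 3: Health impacts): "We will compare trends of health outcomes collected for 3 years pre, and 3 years post implementation (minimum 6 years data".
- Pre-period in the segmented model: from October 2017.
- Go-live: 2022, with no exact date (Table 2).
- Pilot rate: 380 respiratory attendances per week in a subsample of 316,585 (Power calculations).
- Assumed effect: a 5% reduction (Power calculations).

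**Assumptions, not in the protocol**
- *r*, the average fall in attendances during lockdown, shown from 5% to 40%.
- A flat underlying trend.
- The economic comparison taken as a plain difference between pre-period and post-period means.

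**Step 1: the plan's own figure.** Six years of weekly counts give 6 × 52 = 312 points, as stated, so 156 weeks per 3-year period.

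**Step 2: lockdown share of the pre-period, *f*.** 23 March 2020 to 31 July 2021 inclusive is 496 days.
- 3-year window: 496 / 1,096 = 45.3%. A window ending on 1 January 2022 or on 31 December 2022 (starting 31 December 2019) contains the whole lockdown, so the share is the same for any 2022 go-live.
- From 1 October 2017 to 1 January 2022: 496 / 1,553 = 31.9%.
- From 1 October 2017 to 31 December 2022: 496 / 1,917 = 25.9%.

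**Step 3: preparation phase.** August 2021 to a 2022 go-live lasts about 5 to 17 months, all of it counted as pre-implementation.

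**Step 4: apparent effect when the true effect is −5%.** Pre-period mean = 380 × (1 − *f r*). Post-period mean = 380 × 0.95 = 361. Apparent change = 0.95 / (1 − *f r*) − 1.

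| Assumed fall *r* | *f* = 45.3% | *f* = 31.9% | *f* = 25.9% |
|---|---|---|---|
| 5% | −2.8% | −3.5% | −3.8% |
| 10% | −0.5% | −1.9% | −2.5% |
| 20% | +4.5% | +1.5% | +0.2% |
| 40% | +16.0% | +8.9% | +6.0% |

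**Step 5: fall that hides the 5% benefit.** Setting 0.95 / (1 − *f r*) = 1 gives *r* = 0.05 / *f*: 11.0% for the 3-year window, and 15.7% to 19.3% for a pre-period from October 2017.

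**Step 6: in attendances, at the pilot rate over 156 weeks.** The counterfactual contrast gives (380 − 361) × 156 = 2,964 avoided, whatever *r* is, provided the segments are correctly specified. The before/after difference in the 3-year window gives 281 avoided at *r* = 10% and an apparent excess of 2,401 at *r* = 20%.

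**The case against.** The strongest reply is that the comparator sentence names the scenario compared against (no B-CAP) and not the estimator. The protocol describes ITS itself in similar terms, as post-intervention trends compared with earlier ones. Work package 4 takes its data from work package 3, and the long-term model reflects work package 3 sampling uncertainty. The evidence that work package 3 produces is the segmented-regression effect. An article also condenses a fuller plan, so matters such as the price year may properly sit elsewhere.

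Much of this stands. The ITS contrast may well be intended for the health part. A reader might infer that raw, unadjusted means will be compared and the ITS counterfactual set aside. The text does not say that. Nor does it support several further inferences:
- That the results will certainly be biased. Bias follows only if the sentence is applied literally.
- That 45% is the only possible lockdown share. Work package 4 does not define its own pre-period.
- That the planned saving is 2-5%. The protocol expects 5% for attendances; 2% is the reduction it says it has over 90% power to detect.
- That QALYs are biased in a known direction. Fewer attendances during lockdown need not mean better health.

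The reply does not remove the mismatch. The comparator is a stated rule, not an omitted detail. It covers costs as well as outcomes, and work package 3 sets out no model for local-authority or private-economy costs.

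**Conclusion.** The point holds as a mismatch between two stated rules that should be reconciled. Work package 4 compares with the pre-implementation period, work package 3 with a projected no-intervention course, and the text linking them does not say which contrast enters the economic evaluation.

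The consequence is conditional. Under a literal before/after comparison with a flat trend, the assumed 5% benefit in attendances disappears at an average lockdown fall of about 11% (3-year window) or about 16-19% (from October 2017). Larger falls turn it into an apparent increase. The choice of window changes the size of the problem but does not remove it. The result rests on an attendance fall that the protocol does not quantify. It applies to attendance-based NHS use and its cost. For QALYs the direction stays open.

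**What to change.** Restate the work package 4 comparator as the no-B-CAP counterfactual projected by the work package 3 ITS model over the same 3 post-implementation years. Then:
- Take incremental health events, NHS resource use and their costs, overall and by deprivation (IMD) group, as the work package 3 contrast with the same lockdown and preparation segments.
- Carry the uncertainty of that contrast into the within-study analysis as well as the long-term model.
- For local-authority and private-economy costs, which work package 3 does not model, use the incremental costs attributable to the B-CAP and not a before/after difference.
- Show pre-period figures descriptively only, separated by segment, so that the lockdown and preparation phases stay visible.

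The cost is a change of wording and a little extra analysis. For attendance-based outcomes it reuses work package 3 predictions. The downside is that the economic results then depend on the ITS model being correctly specified, including its handling of the lockdown and preparation segments. If the ITS contrast is already intended, one sentence settles the matter for the health outcomes, and the treatment of the other costs still has to be stated.
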